#### Assignment of interventions: blinding {17}

Assessments regarding clinical recovery will be conducted by an assessor blind to treatment allocation. The assessor will go through a profound assessment training program. Due to the nature of the intervention, neither participants nor staff can be blinded to allocation but are strongly inculcated not to disclose the allocation status of the participant at the follow up assessments. An employee outside the research team will feed data into the computer in separate datasheets so that the researchers can analyze data without having access to information about the allocation.

### Data collection and management

#### Plans for assessment and collection of outcomes {18a}

Relevant clinical information and socio-demographic characteristics will be obtained from the hospital information system. Data monitoring committee members and clinical staff will jointly evaluate the collected data. If inappropriate data is found, the research team will be notified to correct the error.

#### Plans to promote participant retention and complete follow-up {18b}

Face-to-face adherence reminder session will take place at the initial informed consent form signing, participants will have an opportunity to ask questions, and key messages from the initial session will be reviewed as needed. All patients will be regularly followed up by staff and will be given priority to make an appointment in the clinic for any emergency.

#### Data management {19}

Data will be stored in encrypted spreadsheets on secured servers hosted by the West China Hospital of Sichuan University. All data collected in this trial will be restricted to the principal investigator and specific members of the research team. The results of this trial will be presented at conferences and published in the form of peer-reviewed journal manuscripts.

#### Confidentiality {27}

The information collected will remain anonymous; participants will be assigned a participant number for identification purposes. The data will be stored in computers that only the research team can access.

#### Plans for collection, laboratory evaluation, and storage of biological specimens for genetic or molecular analysis in this trial/future use {33}

Not applicable. No specimens will be collected.

### Statistical methods

#### Statistical methods for primary and secondary outcomes {20a}

All the data will be recorded in the case report form and data analyses will be done using the SPSS statistical software. Analysis of variance is used for comparing mean values of patients’ age, weight, height, and body mass index. Non-parametric measures are WOMAC, VAS, and IKDC, and differences between baseline and post-treatment scores for each group are computed by the Wilcoxon signed ranks test. The difference between each treatment group is performed by the Kruskal–Wallis test.

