### Objectives {7}

The objective of this study is to assess the effectiveness and safety of utilizing LIFU, TENS, and LIFU combined with TENS after patients underwent PRP for treating KOA in this randomized controlled trial. We will evaluate how well this therapy worked for patients with KOA in terms of pain and physical function. After PRP treatment, it is hoped that the physical stimulation would help patients with knee osteoarthritis experience less pain and functional improvement.

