#### Intervention description {11a}

Eligible subjects screened by inclusion and exclusion criteria will be divided into the control group, and the experimental groups by computer randomization in a random sequence with a ratio of 1:1:1:1. The control group was treated with PRP. The experimental group was treated with PRP with LIFU, PRP with TENS, and PRP with LIFU combined with TENS. Both the experimental group and the control group received PRP treatment three times, with an interval of 4 weeks. The experimental group was treated with LIFU, TENS, and LIFU combined with TENS 24 h after each PRP treatment (the injection needles healed), once a day, for five consecutive days, for a total of three courses of treatment.

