#### Sample size {14}

The sample size of this study was calculated according to the uniform standard of clinical trial report and the requirement of non-inferior experiment sample content. Experimental studies have shown that the minimum clinical significance value of WOMAC scale is 12%. Based on the previous research results of our research team, we set *σ* = 28%, *β* = 0.2, power = 80%, and significance level two-tailed *α* = 0.05. In order to prevent excessive loss of subjects, the shedding rate of 10% was calculated. A total of 120 subjects (27 per group, 4 groups, 10% shedding rate) were required. ITT analysis strategy will be adopted for data analysis. Paired *T*-test analysis will be performed on the evaluation data of OA patients before and after treatment, and variance analysis will be performed on the difference analysis among multiple groups.

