## Discussion

Ultrasound and tens have been wildly used as safe and noninvasive physiotherapy for many years. Through the combination of TENS with ultrasound, patients can simultaneously receive ultrasound waves and electrical stimulation. Although PRP is now used for the treatment of KOA with excellent results, we hope that the physical stimulation can get better results after receiving PRP therapy. To our knowledge, there is no study using physical stimulation after PRP treatment. Therefore, we will conduct this randomized study to evaluate the LIFU, TENS, and LIFU combined TENS with PRP treatment on pain and function in patients with knee osteoarthritis. It is assumed that there will be a difference in outcomes between the intervention and control groups.

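### Before-after tests within each arm are listed beside an omnibus between-arm test with no statement of which decides efficacy; since every arm receives PRP, they cannot show that LIFU or TENS adds anything

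*Protocol article*

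**What the plan says.** The question is what physical stimulation adds to PRP. Objectives {7} sets out to "assess the effectiveness and safety of utilizing LIFU, TENS, and LIFU combined with TENS after patients underwent PRP", and the Discussion states the contrast: "It is assumed that there will be a difference in outcomes between the intervention and control groups". PRP is common to all arms. Intervention description {11a}: "Both the experimental group and the control group received PRP treatment three times, with an interval of 4 weeks".

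Two sections describe the efficacy analysis, and each pairs a within-arm test with a between-arm test:

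- Within arms, the section on statistical methods {20a} plans that "differences between baseline and post-treatment scores for each group are computed by the Wilcoxon signed ranks test". The section on sample size {14} has the parametric counterpart, a paired t-test of scores before and after treatment.
- Between arms, the sample size section plans that "variance analysis will be performed on the difference analysis among multiple groups". The statistical methods section uses a Kruskal–Wallis test for the same purpose.

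Neither section gives one member of the pair priority, calls the within-arm tests descriptive, or names a comparison of an individual add-on arm with PRP alone.

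**The concern.** The null hypothesis of a before-after test is no change from baseline in that arm. The trial needs a test of no difference from PRP alone. On the protocol's own premises the first null should be false even if LIFU and TENS do nothing: the Background cites a sham-controlled trial in which PRP was superior to saline, and the Discussion describes results with PRP as excellent. Placebo response, natural course and regression to the mean act in every arm as well, and the blinding section says that participants know their allocation.

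The between-arm tests answer a question closer to the right one, but as four-group omnibus tests they do not say which arm differs from PRP alone. The before-after tests are thus the only results in these sections that attach to a particular add-on. At stake is a report in which improvement on PRP is credited to LIFU or TENS. It could happen directly, or through the pattern of an add-on arm being significant while PRP alone is not, which is not a test of their difference.

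**Working it through.** **Inputs from Sample size {14}.** Minimum important value 12%, σ = 28%, two-sided α = 0.05, 27 per group before dropout. The dropout step reproduces: 27 / 0.9 = 30 per arm, and 4 × 30 = 120. The protocol states no rejection rate for the within-arm tests, so there is no figure of its own to reproduce on that point.

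**Assumptions, because the documents give no figure.**
- The expected change on PRP is not stated, so a common improvement of 6, 12, 18 or 24 is tried in all four arms, with zero add-on effect.
- The SD of change is not stated. If 28 is the SD of a single score and r is the baseline-to-follow-up correlation, SD of change = 28 × √(2(1 − r)). This gives 33.1 at r = 0.3, 28.0 at r = 0.5 and 21.7 at r = 0.7.
- Changes are normally distributed and arms are independent.

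**Per-arm rejection rate.** Simulated Wilcoxon signed-rank test, 27 per arm:

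| Common improvement | r = 0.3 | r = 0.5 | r = 0.7 |
|---|---|---|---|
| 6 | 15% | 18% | 27% |
| 12 | 43% | 55% | 78% |
| 18 | 76% | 88% | 98% |
| 24 | 94% | 99% | 100% |

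A separate simulation with the SD of change set directly to 28 gave 56% at an improvement of 12. The paired t-test gives nearly the same (about 58%), so the choice between the two tests does not matter here.

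**From one arm to the trial, at improvement 12 and SD of change 28.** With p = 0.556 per arm:
- At least one of three add-on arms significant: 1 − (1 − 0.556)³ = 1 − 0.088 = 0.91. The simulations gave 91–92%.
- At least one add-on arm significant and PRP alone not: 0.912 × (1 − 0.556) = 0.41. The simulations gave 41–42%.

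**Reference.** Kruskal–Wallis on the same simulated changes rejects in about 4–5% of trials, whatever the common improvement. The protocol does not say whether its Kruskal–Wallis test uses post-treatment scores or changes; changes were used here.

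**Why conflicting results are realistic.** For a true two-arm difference of 12 with SD 28 and 27 per arm, the standard error is 28 × √(2/27) = 7.62, and 12 / 7.62 = 1.57. Power is about Φ(1.57 − 1.96) = 35%. Non-significant between-arm results beside significant before-after results are therefore a likely outcome, and the protocol does not say which governs.

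**The case against.** The strongest reply is that the randomised comparison is in the plan. Both sections specify a between-arm test, and it holds its error rate near 5% when the add-ons are inert. Nothing says that the within-arm tests decide efficacy, and being listed first gives a test no priority. The Discussion expects a difference between groups. Ranking analyses is often left to an analysis plan, and this is a condensed article.

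Much of this stands. A reader might infer that the arms are never compared or that the randomised comparison is discarded; the documents do not support that. A reader might also infer that the before-after tests will usually be significant. The documents give neither the expected change on PRP nor its SD, and at an improvement of 6 the per-arm rate is only 15–27%. Nor is 56% an inflated type I error of the planned test. With a true change of 12 it is that test's power, and its own error rate at zero change is about 5%. It becomes a false-positive rate only if the test is read as evidence about the add-on. The Objectives sentence "We will evaluate how well this therapy worked for patients with KOA in terms of pain and physical function" is too loose to show that before-after reasoning is intended.

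The reply does not dispose of what the article positively states. It prescribes before-after significance tests on the efficacy scores in two sections, and the between-arm tests beside them are omnibus. Even if the word each in the Kruskal–Wallis sentence is read generously, that method is one test across four groups and yields no contrast of an add-on with PRP alone.

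**Conclusion.** The point holds in a limited form. The planned within-arm tests cannot show that LIFU, TENS or their combination adds to PRP, yet they are the only arm-specific tests named, and the protocol does not say that the between-arm comparison decides. That logic follows from the design and needs no numerical assumption.

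The size is conditional. If all arms improve by the protocol's own minimum important value of 12, with SD of change 28 and 27 per arm, inert add-ons would still give about 56% significance per arm, about 92% for at least one add-on arm, and about 41% for the misleading add-on-but-not-PRP pattern. Across r = 0.3–0.7 the per-arm rate runs from 15–27% at an improvement of 6 to 76–100% at 18 or more. This should be corrected, but the plan does contain a valid between-arm test to build on.

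**What to change.** Keep the between-arm analysis. In both Sample size {14} and Statistical methods {20a}, state that conclusions about LIFU, TENS and the combination rest only on the randomised difference of each add-on arm from PRP alone, analysed on change or adjusted for baseline, with its 95% confidence interval. Report each arm's change from baseline with a confidence interval, labelled descriptive and not used as an efficacy test. Add that significance in one arm but not in another will not be read as a treatment effect. Rewording the Objectives to refer to improvement over PRP alone is optional.

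This changes wording in two sections and needs no extra patients, visits or data. The cost is that before-after p-values can no longer be offered as evidence of efficacy.

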#### Methods for additional analyses {20b}

Currently, there is no planned additional subgroup or adjusted analyses.

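### Two different sets of tests are stated for the same efficacy scores, with no rule for which governs, the compared score (change or follow-up) unstated, and no baseline-adjusted analysis planned

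*Protocol article*

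**What the plan says.** The Protocol article states the efficacy analysis in two places.

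- **Sample size {14}:** for change within patients, "Paired *T*-test analysis will be performed on the evaluation data of OA patients before and after treatment". For the comparison of the arms, this section adds that "variance analysis will be performed on the difference analysis among multiple groups".
- **Statistical methods for primary and secondary outcomes {20a}:** "Non-parametric measures are WOMAC, VAS, and IKDC". For these, "differences between baseline and post-treatment scores for each group are computed by the Wilcoxon signed ranks test". The arms are then compared by a rank test as well: "The difference between each treatment group is performed by the Kruskal–Wallis test". Analysis of variance appears here only for patient characteristics: "Analysis of variance is used for comparing mean values of patients’ age, weight, height, and body mass index".

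On adjustment, **Methods for additional analyses {20b}** says: "Currently, there is no planned additional subgroup or adjusted analyses".

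The sizing in {14} rests on a minimum important WOMAC value of 12%, σ = 28%, 80% power and two-sided α = 0.05. Scores are taken before each PRP treatment and at 3 and 6 months after the course (Outcomes {12}). The Abstract names VAS as primary; Outcomes {12} names WOMAC.

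**The concern.** These are two answers to one question, not a detail left for an SAP. The same scores get parametric tests in one section and rank tests in the other, and no normality check or other rule links them as alternatives. Whoever runs the analysis could follow either section and claim to have followed the protocol.

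Three consequences follow.

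1. The p-value for the main comparison depends on which section is followed, and also on whether follow-up or change scores are entered, which neither section fixes.
2. The trial is sized on a mean difference and an SD. Kruskal–Wallis is an omnibus rank test, so it returns no mean difference or confidence interval to hold against 12%.
3. The baseline score is collected, but no analysis is planned that uses it as a covariate. In groups of about 27, that gives up precision and leaves chance baseline imbalance without a covariate adjustment.

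The before/after tests within each arm, present in both versions, do not estimate the randomised comparison with PRP alone.

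**Working it through.** **Step 1. The two sections side by side.**

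| Comparison | Sample size {14} | Statistical methods {20a} |
|---|---|---|
| Before/after, within group | Paired t-test | Wilcoxon signed-rank |
| Between groups | Analysis of variance | Kruskal–Wallis |
| Role of ANOVA | Evaluation data | Age, weight, height, BMI only |
| Score compared between groups | Not clear | Not stated |
| Baseline as covariate | No | No |

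The conflict does not depend on which outcome is primary, because both sets of tests are stated for the scores generally.

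**Step 2. The plan's own figure.** The dropout step reproduces: 27/0.9 = 30, and 4 × 30 = 120. The 27 does not. For two means, n = 2 × [28 × (1.960 + 0.842)/12]² = 85.5, so 86 per arm. That is a separate point. It matters here only because 27 per arm is the planned evaluable number used below.

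**Step 3. Effect of an open choice on type I error.** Simulation under no treatment effect, with 4 groups of 27, normal data, 8,000 runs at each assumed baseline-to-follow-up correlation r:

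| r | ANOVA on change | Kruskal–Wallis on change | Better of these two | Better of ANOVA on change and Kruskal–Wallis on follow-up |
|---|---|---|---|---|
| 0.3 | 5.0% | 4.8% | 5.9% | 8.3% |
| 0.5 | 4.8% | 4.4% | 5.7% | 8.7% |
| 0.7 | 5.3% | 5.1% | 6.2% | 9.5% |

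On the same change scores, the two tests disagree at 0.05 in about 2% of trials. Simulation error is about 0.3 percentage points, from √(0.06 × 0.94/8000) = 0.0027. Most of the inflation comes from the score type, not from the choice of test.

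**Step 4. Precision from baseline adjustment.** The article does not give r, so it is an assumption. It also does not say whether 28 is the SD of follow-up scores or of change, so both readings are shown. With equal variances at baseline and follow-up, and follow-up SD σ:

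- follow-up only: variance σ²
- change: 2(1 − r)σ²
- ANCOVA: (1 − r²)σ²
- ANCOVA relative to change: (1 − r²)/[2(1 − r)] = (1 + r)/2

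Power for one pairwise comparison, difference 12, 27 per arm, two-sided 0.05, no multiplicity correction: Φ(12/[SD × √(2/27)] − 1.96). For follow-up scores with SD 28 this is Φ(12/7.62 − 1.96) = Φ(−0.385) = 35%.

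| r | If 28 is follow-up SD: follow-up only | Change (SD) | ANCOVA (SD) | If 28 is SD of change: change | ANCOVA (SD) |
|---|---|---|---|---|---|
| 0.5 | 35% | 35% (28.0) | 44% (24.2) | 35% | 44% (24.2) |
| 0.6 | 35% | 42% (25.0) | 50% (22.4) | 35% | 42% (25.0) |
| 0.7 | 35% | 53% (21.7) | 60% (20.0) | 35% | 40% (25.8) |

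These use the normal approximation. The t distribution lowers each by one to two points: 34% for follow-up only, and 43, 49 and 58% for ANCOVA on the first reading. ANCOVA has the smaller variance for every r strictly between 0 and 1, but the size of the gain depends on both unknowns.

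**The case against.** The strongest reply is that {20a} is the section headed for primary and secondary outcomes, so a reader may take it as governing and the sentences in {14} as stray. That is a natural guess, but the document does not say so, and {14} is where the mean-based target is set.

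A second reply is that Kruskal–Wallis, ANOVA and change-score comparisons are all valid under randomisation, and that covariates are often left to an SAP. This stands. Lack of ANCOVA is a loss of efficiency, not an error, and the contradiction is the firmer half of the point.

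A third is that the Blinding section {17} has the researchers analyse without access to allocation. That limits steering towards a favoured arm. It does not stop anyone seeing which test crosses 0.05.

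Three stronger readings are tempting and are not supported.

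- *Both plans ignore baseline.* Both sections speak of differences and can be read as comparing change between groups, which uses baseline by subtraction. What can be said is that neither uses it as a covariate and neither fixes the score.
- *Adjusted analyses are barred.* Section {20b} says only that "there is no planned additional subgroup or adjusted analyses", under a heading on additional analyses and qualified as the current position.
- *The within-group tests are the primary analysis.* They are mentioned first, but both sections also give a between-group test, and neither ranks them.

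**Conclusion.** The point holds. Sections {14} and {20a} assign different tests to the same efficacy scores, no rule says which governs, and the between-group score is not fixed. If the choice were made after seeing the data, type I error would be about 6% on the same change scores, and about 8 to 9.5% between ANOVA on change and Kruskal–Wallis on follow-up. These figures assume normal data and describe what the text leaves open. Nothing in the article says that anyone intends to choose that way.

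The missing covariate adjustment is on the page and costs precision. Only the direction is certain. For r of 0.5 to 0.7, ANCOVA power at 27 per arm is about 43 to 60% if 28 is the follow-up SD, against about 35% for follow-up scores and 35 to 53% for change scores. It is about 40 to 44% against 35% if 28 is the SD of change, and then the gain shrinks as r rises. A reader might quote the rise from about 35% to nearly 60% as the gain, but that is the favourable case: follow-up SD, r = 0.7, and follow-up scores alone as the comparator.

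Nor does adjustment rescue the sample size. Even at r = 0.8 with 28 as the follow-up SD, ANCOVA needs 31 per arm, from 85.5 × (1 − 0.64) = 30.8.

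**What to change.** State one primary between-group analysis, in the same words, in {14}, {20a} and {20b}:

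1. Reconcile the primary outcome (VAS in the Abstract, WOMAC in Outcomes {12}) and name one primary visit. Without both, aligning the tests still does not give a single analysis.
2. Use ANCOVA, or a repeated-measures mixed model, for that outcome, with treatment group and the baseline score as covariate. This also settles the question of change or follow-up score.
3. Report adjusted mean differences of each add-on arm against PRP alone with 95% confidence intervals, so that they can be set against the 12% threshold.
4. Make the rank test a sensitivity analysis and the within-group before/after tests descriptive.
5. Amend {20b} so that it no longer conflicts with a baseline-adjusted primary model, and say in {14} whether σ = 28% refers to follow-up scores or to change.

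The cost is a wording amendment. The baseline scores are already collected and the models run in the planned SPSS software. It should be settled before anyone sees outcome data by group.

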**Methods:**

This is a protocol paper that outlines a randomized controlled trial, patients will be assigned randomly to the PRP group, PRP+LIFU group, PRP+TENS group, and PRP+LIFU combined TENS group. The patients will be followed at 12-week and 24-week time points to evaluate the primary and secondary outcomes of the study. The primary outcome is the VAS pain score. Secondary outcomes include Western Ontario and McMaster Universities Osteoarthritis Index (WOMAC) and International Knee Documentation Committee scores (IKDC). After baseline examination, all patients will sign a written informed consent for study participation after a full explanation of the treatment protocol. We have planned a total of 120 patients (30 patients per group).

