#### Assignment of interventions: allocation {16}

Randomization will be performed by simple randomization method using software-generated numbers before the study begins. Participants will be randomly assigned to one of the four groups in a ratio of 1:1:1:1. As the service will not release the randomization code until the patient has been recruited into the trial, which takes place after all baseline measurements have been completed, randomization will be completed by the staff member who not involved in the assignment or care of the trial participants will be used to assign participants to which group.

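### The objective asks whether LIFU, TENS and their combination each improve on PRP alone, but every stated between-group test is omnibus and cannot answer that

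*Protocol article*

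**What the plan says.** Objectives {7} sets out to "assess the effectiveness and safety of utilizing LIFU, TENS, and LIFU combined with TENS after patients underwent PRP for treating KOA". Under Intervention description {11a} the control group receives PRP, and "The experimental group was treated with PRP with LIFU, PRP with TENS, and PRP with LIFU combined with TENS". Allocation {16} is equal: "Participants will be randomly assigned to one of the four groups in a ratio of 1:1:1:1". The Discussion expects outcomes to differ between the intervention groups and the control group.

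The efficacy tests named are these:

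- **Between groups, Statistical methods {20a}:** "The difference between each treatment group is performed by the Kruskal–Wallis test".
- **Between groups, Sample size {14}:** "variance analysis will be performed on the difference analysis among multiple groups".
- **Within groups, {20a}:** "differences between baseline and post-treatment scores for each group are computed by the Wilcoxon signed ranks test". Sample size {14} names a paired t-test for the same purpose.

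Section {20b} plans no additional subgroup or adjusted analyses. The protocol article states no comparison of a given arm with PRP alone.

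**The concern.** The objective contains three questions, one for each active arm against PRP alone. A four-group test with 3 degrees of freedom answers a different one: whether all four distributions are the same. If it rejects, the protocol states no step from that result to a claim about LIFU, TENS or the combination, and no effect estimate.

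The before-after tests do not fill the gap. Every arm receives PRP, so an improvement from baseline in the PRP+LIFU arm mixes the effects of PRP, of LIFU and of time. A significant change in one arm and a non-significant change in another is not a comparison of the two.

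At stake is how the result will be read. With only an omnibus p-value and four before-after p-values planned, any statement about a particular device would rest on comparisons chosen after the data are seen.

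**Working it through.** **1. Can the omnibus test separate the answers that the objective needs?** Take mean improvements over PRP alone in the order PRP, PRP+LIFU, PRP+TENS, PRP+both, with 12% as the effect.

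- Only the combination works: (0, 0, 0, 12). Mean 3; sum of squares about the mean 9 + 9 + 9 + 81 = 108.
- Each device works alone and the combination adds nothing: (0, 12, 12, 12). Mean 9; sum of squares 81 + 9 + 9 + 9 = 108.

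The noncentrality of the analysis of variance is 27 × 108 / 28² = 3.72 in both cases, so power is the same (32%). Kruskal–Wallis also has about the same simulated power for both, roughly 30%. The test does not distinguish two opposite clinical conclusions.

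**2. Inputs.** From Sample size {14}: difference 12%, SD 28%, two-sided alpha 0.05, power 80%, 27 evaluable per group, 10% dropout. I assume that the SD applies to the score analysed and that no baseline adjustment is made.

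**3. The plan's own figure.** n per group = 2 × (1.960 + 0.842)² × (28/12)² = 2 × 7.849 × 5.444 = 85.5, so 86, not 27. Reading it as non-inferiority with a 12% margin at one-sided 0.025 also gives 86. Four-group analysis of variance gives 31 to 120 per group for the mean patterns tried: (0, 12, 12, 24) needs 31 and (0, 6, 6, 12) needs 120. Only the dropout step reproduces: 27/0.9 = 30, and 30 × 4 = 120.

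**4. Power of comparisons that would answer the objective, 27 per arm.**

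| Contrast | SE | 12/SE | Alpha | Power |
|---|---|---|---|---|
| One active arm v PRP | 28√(2/27) = 7.62 | 1.57 | 0.05 | 34% |
| Same, Dunnett for three (critical value about 2.38) | 7.62 | 1.57 | familywise 0.05 | 22% |
| Main effect, 54 v 54 | 28√(2/54) = 5.39 | 2.23 | 0.05 | 60% |
| Same, two main effects | 5.39 | 2.23 | 0.025 | 48% |
| Interaction of 12 | 28√(4/27) = 10.78 | 1.11 | 0.05 | 20% |

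Powers are from the noncentral t distribution. The normal approximation gives 35.0% for the first row and 60.5% for the third. The main-effect rows assume no interaction.

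**5. Size needed for 80% power, before multiplicity correction.** Arm against control: 86 per arm, 344 evaluable, and 86/0.9 rounded up to 96, × 4 = 384 enrolled. Main effects: 43 per arm, 172 evaluable, and 43/0.9 rounded up to 48, × 4 = 192 enrolled.

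**6. Omnibus against one main effect (simulation, normal data, no baseline adjustment, main effect at uncorrected 0.05).**

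| True pattern | Kruskal–Wallis | LIFU main effect |
|---|---|---|
| Only LIFU works, +12 | 40% | 60% |
| Both work additively, +12 each | 71% | 60% |
| Only the combination works, +12 | about 30% | about 20% |

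The ranking depends on the pattern, so power alone does not decide against the omnibus test. What decides is that its rejection identifies no intervention.

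**The case against.** The best defence is that contrasts and multiplicity rules are commonly left to an analysis plan, which is not shown here. That stands against any complaint of missing detail. It does not meet this point: {20a} assigns the comparison between treatment groups to Kruskal–Wallis, which cannot do that job for this objective, and {14} names a different omnibus test.

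Three stronger readings are tempting, and the documents do not support them.

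- **That half the information goes unused.** A reader may infer this from the 2×2 layout. Kruskal–Wallis uses all four arms. The factor of two is the variance ratio of a pairwise contrast to a main effect (7.62² / 5.39² = 2). It needs little interaction, and the protocol states no pairwise contrast.
- **That the trial must be analysed as a factorial.** The protocol never calls it one. It speaks of a control group and experimental groups. A main effect averages over the other device and does not answer the question about the combination. If only the combination works, some Holm-corrected main effect is significant about 24% of the time, against about 30% for Kruskal–Wallis.
- **That the plan inflates the type I error.** Uncorrected, three comparisons with control would carry about 12% familywise error and all six pairs about 20%. The protocol states no such tests, so these figures show a risk of unplanned testing, not a property of the plan.

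**Conclusion.** The point holds as a mismatch between the stated objective and the stated tests. Both named between-group analyses are omnibus, they disagree with each other on method, and neither shows which intervention improves on PRP alone or by how much. The within-group tests cannot separate a device from PRP.

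The remedy does not rescue power. At the plan's own inputs, one comparison with control has about 34% power, or 22% with Dunnett. A main effect has about 60%, or 48% at alpha 0.025. These figures rest on 27 evaluable per arm, an SD of 28% for the analysed score and approximate normality. They concern WOMAC, for which {14} gives its inputs. The abstract names VAS as primary and Outcomes {12} names WOMAC, so they may not describe the outcome finally taken as primary.

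**What to change.** 1. In {20a}, make the primary between-group analysis three prespecified comparisons: PRP+LIFU, PRP+TENS and PRP+LIFU+TENS, each against PRP alone. Control the familywise error with Dunnett's procedure or, if ranks are kept, pairwise rank tests with Holm. Report each difference with a confidence interval.
2. Keep one omnibus test as supportive only, and describe the before-after tests as descriptive.
3. Make the analysis wording in {14} agree with {20a}.
4. Optionally add the LIFU and TENS main effects and their interaction as secondary estimates. State that the main effects assume little interaction and that the interaction will be imprecise (about 20% power for 12%).
5. Restate the power in {14} for the comparisons actually chosen.

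Items 1 to 4 need an amendment before the data are analysed, and no extra patients. The cost is that item 5 will show power well below 80% with 120 patients. The sponsor must then either justify different inputs, enlarge the trial, or present the comparisons as estimates with wide intervals: about ±15% per comparison before adjustment (1.98 × 7.62) and ±18% with Dunnett (2.38 × 7.62).
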